#### Immunologic objectives

Secondary objectives also include the evaluation of the effects of preleukapheresis IFN-α on DC yield and potency, and of maturation-induced TEM8 expression on DC:

a) DC yield: the number of DC obtained per ml of blood processed by leukapheresis will be recorded at each leukapheresis and compared between the different treatment arms (IFN-α vs no-IFN-α);

b) DC potency: DC vaccine potency will be analyzed using an ELISPOT-based version of the COSTIM assay which will evaluate the co-stimulatory ability of dendritic cells;

c) TEM-8 upregulation observed upon DC maturation in non-immunoresponsive patients will be evaluated by qRT-PCR and the distribution of TEM-8 mRNA iDC: mDC ratio will be compared between the different treatment arms (IFN-α *vs* no-IFN-α). The percentage of patients in each treatment group reporting an adverse event (AE) up to 30 days after vaccination will be tabulated with 95% confidence intervals according to type of AE. The overall rate of grade 3–4 AEs will be calculated on the basis of treatment group. In addition, summary statistics of clinically significant laboratory abnormalities will be tabulated.

### Overview of study phases

#### Screening

Before entering the study, patients will be required to undergo tumor tissue collection according to Good Manufacturing Practice (GMP) guidelines, as per current Standard Operating Procedures of the IRST Laboratory of Somatic Cell Therapy (STC Lab) (Figure 1). Tumor tissue will be stored in the Therapeutic Cell Bank of the STC Lab until use for vaccine manufacturing. Only patients from whom autologous tumor tissue has been collected by the STC Lab under GMP will be eligible for the study. After informed consent has been obtained, patients will enter the screening phase (tumor staging and clinical and laboratory assessments) to determine their eligibility for the trial. In particular, patients must have at least one measurable and one non-measurable lesion.

**Figure 1 F1:**
[figure not shown]
Induction and maintenance phase schedule.

#### Leukapheresis and vaccine manufacturing

At the end of the screening phase, patients will be randomized and will enter the leukapheresis and vaccine manufacturing phase. Each patient will be assigned to one of the following arms:

(1.) three daily doses of 8 Gy - 12 Gy radiotherapy delivered to one non-index metastatic field (optional to one additional field) between vaccine doses 1 and 2 and between doses 7 and 8, using IMRT-IMAT techniques;

(2.) daily 3 MU subcutaneous IFN-α for 7 days before leukapheresis;

(3.) both 1 and 2 external immunostimulant conditions;

(4.) neither 1 nor 2 external immunostimulant conditions.

At least six patients eligible for treatment will be enrolled per arm.

#### Induction

After vaccine preparation, the patients will start treatment in the induction phase. Before the first dose of the vaccine (day 1), patients will undergo blood sampling for immunological markers (quantification of circulating tumor-specific immune effectors) and the baseline DTH test. Three MU IL-2 will be administered subcutaneously daily for five days starting from the second day after each vaccine dose. Vaccine doses will be given intradermally in two sites close to inguinal or axillary lymph node stations that have not been the site of previous surgical exeresis. The first dose (wk1) will consist of the freshly prepared vaccine, whereas cryopreserved aliquots will be used for all other doses. The second dose will be administered after three weeks (wk4) to allow for the completion of quality assurance/quality control (QA/QC) assessments on the cryopreserved vaccine batches that will be used across all further phases. The remaining two doses of the induction phase will be administered after a 2-week interval (wk6 and wk8). At wk2, patients randomized to receive RT will undergo the planned treatment: one non-measurable (or non-index measurable, if available) lesion will be irradiated using IMRT-IMAT techniques to facilitate tumor antigen release and and antigen uptake by intratumoral DC under “danger” conditions created by ionising radiation, thus potentially boosting immunization induced by the DC vaccine. The remaining measurable lesion (s) will be used as an index lesion (s) to evaluate objective response according to irCR.. The induction phase will end with tumor restaging, blood sampling for immunological biomarkers and DTH test (the day before wk12 vaccine dose).

#### Maintenance

Patients showing irCR, irPR or irSD or non-confirmed irPD will enter the maintenance phase during which they will receive further vaccine doses at four-week intervals until irPD is confirmed, for up to a maximum of 14 vaccinations (wk48). Tumor assessments, blood sampling for immunological biomarkers and DTH tests will be performed every 12 weeks (wk24, 36 and 48).

In the event of vaccine shortage, patients will undergo additional leukapheresis at least two weeks after the last RT (according to treatment arm) and at least one week before the next vaccine dose: patients assigned to the IFN-α arms will repeat this treatment for seven days before leukapheresis with the same schedule and dosage. Patients undergoing additional leukapheresis must have negative tests for HBV, HCV, HIV and treponema not dating back more than 30 days. This procedure will be performed to facilitate the completion of the QA/QC assessment on the new cryopreserved vaccine batch. At week 22 (between vaccine doses V7 and V8), patients randomized to RT can optionally repeat this treatment on a non-index, not previously irradiated lesion, if available. On the basis of irCR, patients showing irPD will continue treatment until confirmation of progression. Patients with confirmed irPD showing positive DTH may, at the physician’s discretion, continue treatment until the next tumor assessment. If, at the next re-staging, further progression is observed, these patients will be discontinued.

### Study population

Patients with unresectable stage III or stage IV melanoma with at least two measurable lesions who may or may not have undergone previous lines of specific therapy (i.e. chemotherapy, immunotherapy, targeted therapy, etc.).

#### Inclusion criteria

(1.) Signed written informed consent: patients must be willing and able to give written informed consent and this must be provided before starting the screening procedure;

(2.) Availability of autologous tumor tissue that fulfils acceptance criteria

(3.) Patients must have histologically or cytologically confirmed malignant unresectable stage III or stage IV melanoma (any type considered);

(4.) Patients must have a minimum of two lesions, one of which must be accurately measurable in two perpendicular dimensions (at least one diameter >20 mm and the other dimension >10 mm) using or at least 10 × 10 mm using spiral CT scan;

(5.) Patients carrying BRAF mutation-positive melanoma must have received previous vemurafenib unless they are not eligible for or have refused treatment;

(6.) Patients treated with previous first-line therapy must have received ipilimumab unless they are not eligible for or have refused treatment;

(7.) Pre-treated brain metastases that have been clinically stable for at least six months and that do not require corticosteroids are allowed;

(8.) ECOG performance status 0–1;

(9.) Negative screening tests for HIV, HBV, HCV and syphilis not dating back more than 30 days before any of the GMP-regulated activities required are performed (leukapheresis, collection of tumor biopsies to be used for tumor lysate/homogenate preparation);

(10.) Prior lines of chemotherapy, immunotherapy or biological therapy (e.g. inhibitors of BRAF or c-Kit, ipilimumab, etc.) for advanced disease are allowed (patients must have completed prior treatments at least four weeks before the first vaccine dose);

(11.) Males and females aged 18–70 years;

(12.) Females of childbearing potential (WOCBP) must use an adequate method of contraception to avoid pregnancy throughout the study and for eight weeks after the study to minimize the risk of pregnancy;

(13.) Patients must have normal organ and marrow function as defined below:

– leukocytes >1,500/μL;

– absolute neutrophil count >1,000/μL;

– platelets >80,000/μL;

– total bilirubin ≤ 2 × ULN;

– AST (SGOT)/ALT (SGPT) <2.5 × ULN;

– creatinine ≤ 2 mg/dl.

#### Exclusion criteria

Participants will not be eligible for the study if ANY of the following apply:

(1.) Patients with positive tests for HCV, HBV, HIV or syphilis (specific blood testing must be performed no more than 30 days prior to any GMP regulated activity (leukapheresis and collection of tumor biopsies to be used for tumor lysate/homogenate preparation);

(2.) Patients with unresectable or metastatic BRAF V600 mutation-positive melanoma eligible for vemurafenib may not be enrolled for first-line treatment;

(3.) Patients eligible for ipilimumab treatment can only be given the drug as first-line treatment;

(4.) Patients who have had chemotherapy or radiotherapy in the four weeks prior to entering the study or those who have not recovered from adverse events caused by treatment administered more than four weeks earlier;

(5.) Participation in another clinical trial with any investigational agent in the 30 days prior to study screening;

(6.) Patients with known progressing and/or symptomatic brain metastases;

(7.) Uncontrolled intercurrent illness including, but not limited to, ongoing or active infection, symptomatic congestive heart failure, unstable angina pectoris, cardiac arrhythmia or psychiatric illness/problems in social situations that would limit compliance with study requirements (at the physician’s discretion);

(8.) Other known malignant diseases in the patient’s medical history with a disease-free interval of less than three years (except for previously treated basal cell carcinoma and in situ carcinoma of the uterine cervix);

(9.) Any contraindication, in the opinion of the blood transfusionist, to undergo leukapheresis (*e.g*. severe anaemia, thrombocytopenia, oral anticoagulant therapy).

### Clinical endpoint assessments

#### Tumor assessment

This study will use immune-related response criteria (irRC) [47], which is a further refinement of modified WHO (World Health Organization) criteria, to better describe tumor response in subjects undergoing immunotherapy (Table 1). irRC were created because of the natural history of clinical response observed in subjects treated with immunological agents such as ipilimumab, which differ from those experienced by individuals receiving other classes of anti-cancer agents.

**Table 1 T1:** **Immune**-**response response criteria** (**irRC**)

**Index lesions**	**Non-****index lesions**	**New measurable lesions**	**New non**-**measurable lesions**	**% Change in tumor burden**	**irRC-****overall response**
CR	CR	No	No	−100%	irCR
PR	Any	Any	Any	≥ -50%	irPR
PR	Any	Any	Any	< -50% to < +25%	irSD
PR	Any	Any	Any	≥ +25%	irPD
SD	Any	Any	Any	< -50% to < +25%	irSD
SD	Any	Any	Any	≥ +25%	irPD
PD	Any	Any	Any	≥ +25%	irPD
SD	Any	Any	Any	< -50% to < +25%	irSD
SD	Any	Any	Any	≥ +25%	irPD
PD	Any	Any	Any	≥ +25%	irPD

*irRC*: immune-related response criteria; *PR*: partial response; *SD*: stable disease; *PD*: progressive disease.

The main differences between irRC criteria and conventional criteria are:

– new measurable lesions are incorporated into the tumor burden (*e.g*. added to the index lesions) and do not define progression unless the total measurable tumor burden increases by the required amount of 25%;

– new non-measurable lesions (including bone lesions) are not considered progression if the total measurable tumor burden is stable or shrinking;

– changes in non-measurable lesions only contribute to the definition of irCR;

– disease progression must be confirmed.

### Immunologic endpoint assessment

#### Immunologic efficacy

Immunologic efficacy, *i.e*. the ability of the different treatments to efficiently induce an anti-tumor immune response, will be measured by the DTH test against ATL and KLH after at least four vaccine induction doses. DTH testing will be performed in all patients on day −1 (*pre*-*treatment DTH*, which showed no reactivity in the vast majority of patients evaluated in our previous studies), and one day before the 5th, 8th, 11th and 14th vaccine dose (*post*-*treatment DTH*). Scalar doses (100, 50, 20, 10 and 5 μg) of autologous tumor lysate and KLH (pulsed into DC together with tumor lysate as an adjuvant) will be used. The diameter of the induration/erythema observed after 24 hours will be recorded according to the following scale: 0–5 mm grade 1, 6–10 mm grade 2, 11–20 mm grade 3, >21 mm grade 4. As DTH reactivity to lower concentrations of the antigen (s) is closely related to more intense antigen-specific immune response, the score results will be normalized against the concentration itself and transformed into a 0–80 scale for analysis purposes.

The best result obtained for each patient at any of the post-treatment DTHs, either for ATL or KLH, will be taken into account for data analysis (best normalized score). The best normalized score distributions across the different treatment arms will be evaluated according to non-parametric tests and, if the differences are found to be statistically significant, the specific primary objective will be considered fulfilled.

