#### ELISPOT analysis

IFN-γ-ELISPOT assay will be performed using a commercial kit (Tema Ricerca, Bologna, Italy) according to the manufacturer’s instructions. Total PBMCs (10^5^ cells/well) will be used as responding cells and stimulated with 1 μg/mL of peptide covering the entire set of tumor antigens known to be expressed in melanoma (tyrosinase, MART1, MAGEA3, MAGEA1, gp100, NY-ESO, SOX2 and survivin; JPT GmbH, Germany). Plates will be evaluated by a computer-assisted ELISPOT reader (Eli.Expert, A.EL.VIS, Hannover, Germany). The patients’ DTH scores will also be evaluated in combination with IFN-γ-ELISPOT analysis of tumor antigen-specific circulating effectors in the different treatment arms with the same time schedule. In particular, if no significant difference across the treatment arms is found for DTH testing, the distribution of the fold increase (*i.e*. the post-vaccine: pre-vaccine ratio values) in Spot Forming Cells (SFC)/100,000 total PBMC recorded after at least four vaccine doses compared to pre-vaccine values, obtained by ELISPOT analysis and after subtraction of SFC observed in non-stimulated PBMC, will be evaluated using the Student’s t-test across the different treatment arms. If differences are found to be statistically significant (significance level 0.05), the specific primary objective will be considered fulfilled.

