### Sample size

This is a “randomized selection design” study based on the assumption that immunotherapy is expected to be effective only in patients showing efficient induction of antitumor immune responses (“targeted endpoint”) [49]. The Steinberg and Venzon approach permits the researcher to select one among a number of different treatment arms as being worthy of further evaluation in a subsequent study. This method requires an adequate gap in the number of immune responses among different arms be observed in order to limit the probability that the selected arm is, in actual fact, inferior to the others. Assuming an error probability of selecting an inferior arm of 10%, a gap of 2 patients with an immune response out of a total of 6 enrolled patients per arm is sufficient, regardless of the proportion of irOR expected in each arm, to show that the difference between the highest probability of response and the best response of the remaining arms is 15%. If the gap is inferior to 2 patients, no treatment arm can be considered better than another and new immunostimulating therapies will have to be identified to combine with the DC vaccine.

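### The DTH endpoint is meant to capture induced immunity, but its score ignores the pre-vaccine DTH test that every patient has

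*Protocol article*

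**What the plan says.** All statements are in the protocol article.

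- **Aim.** Under *Immunologic efficacy*, the endpoint is "the ability of the different treatments to efficiently induce an anti-tumor immune response". The primary *Immunologic objective* likewise speaks of DTH development.
- **Baseline test.** "DTH testing will be performed in all patients on day" −1, and again one day before doses 5, 8, 11 and 14. *Induction* confirms blood sampling "and the baseline DTH test" before the first dose. On prior reactivity the text says only "which showed no reactivity in the vast majority of patients evaluated in our previous studies".
- **Analysed score.** "The best result obtained for each patient at any of the post-treatment DTHs, either for ATL or KLH, will be taken into account". Scores are normalized to antigen concentration and put on a 0–80 scale. Their distributions are compared across arms by non-parametric tests, and significance fulfils the objective. No subtraction, ratio, covariate or exclusion uses the day −1 result.
- **ELISPOT.** If DTH shows no difference, ELISPOT is analysed as a fold increase, that is "the post-vaccine: pre-vaccine ratio values".
- **Selection rule.** *Sample size* requires "a gap of 2 patients with an immune response out of a total of 6 enrolled patients per arm". *Trial design and statistical considerations* lets the immunological endpoint guide the choice, by the same method, when irDCR does not settle it.
- **Eligibility.** Prior immunotherapy is allowed, and no criterion excludes patients who are DTH-reactive before vaccination.

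**The concern.** The stated aim is a change produced by treatment, but the variable is a level reached after treatment. A patient who reacts on day −1 and still reacts later gets the same score as a patient converted by the vaccine. The text accepts that such patients exist, collects the measurement that would identify them, and does not use it. Two measures of one objective are therefore built differently: ELISPOT, used as the fallback, is referenced to baseline, while DTH, which is tested first, is not.

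With six patients per arm, randomization balances pre-existing reactivity in expectation but not reliably in any one trial. If the post-only score also decides who counts as an immune response under the gap rule, pre-existing reactivity moves all arms towards a common higher rate, and a truly better arm is harder to separate from the rest.

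The score is fixed in the text, so this is not a detail left to the analysis plan.

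**Working it through.** **1. The plan's own figure.** Inputs from *Sample size*: 6 per arm, gap of 2, difference of 15 points, at most 10% chance of selecting an inferior arm. By exact binomial enumeration, with the inferior rate scanned from 0 to 0.85, the largest probability that an inferior arm leads by 2 or more is 8.1% with two arms and 8.6% with four arms (three equally inferior). The stated 10% limit is reproduced.

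**2. How many pre-reactive patients.** The document gives no share, so b = 5% and 10% are assumptions.
- Expected among 24 patients: 24b = 1.2 and 2.4.
- Chance of at least one: 1 − (1 − b)^24 = 71% and 92%.
- A classification changes only if the patient would not have been immunized anyway. *Dendritic cell vaccination* says two-thirds of patients respond. If that also holds for pre-reactive patients, the expected number of changed classifications is 24b/3 = 0.4 and 0.8, and the chance of at least one is 1 − (1 − b/3)^24 = 33% and 56%.

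**3. Effect on the gap-of-2 rule.** Assume that the count uses the post-only score and that pre-reactivity is independent of conversion. A true induced rate p then appears as 1 − (1 − p)(1 − b). Let f and F be the probability and cumulative probability of the count in each of three equal arms, and g and G the same for the best arm.
- Correct selection = Σ_j g(j)·F(j − 2)³.
- Wrong selection = 3·Σ_i f(i)·F(i − 2)²·G(i − 2).

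| True rates | b | Apparent rates | Correct | Wrong |
|---|---|---|---|---|
| 65% v 50/50/50% | 0 | 65.0 v 50.0% | 13.6% | 7.8% |
| | 5% | 66.75 v 52.5% | 12.6% | 7.8% |
| | 10% | 68.5 v 55.0% | 11.6% | 7.6% |
| 80% v 50/50/50% | 0 | 80.0 v 50.0% | 30.6% | 2.6% |
| | 5% | 81.0 v 52.5% | 27.9% | 2.7% |
| | 10% | 82.0 v 55.0% | 25.1% | 2.7% |

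The 65% scenario uses the plan's 15-point difference. The 80% scenario is a larger effect chosen for illustration.

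**4. Effect on the rank test.** Illustrative Kruskal-Wallis simulation: 6 per arm, assumed scores, 67% induced in every arm under the null, and one arm raised by 33 points under the alternative.

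| Pre-reactive | Type I error, post-only / change | Power, post-only / change |
|---|---|---|
| 0% | 4.3% / 4.3% | 11.2% / 11.2% |
| 10% | 3.6% / 4.0% | 9.1% / 10.4% |
| 20% | 4.0% / 4.0% | 8.4% / 10.0% |

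**5. What a change score can recover.** The b = 0 rows are reached only if pre-reactive patients show an increase as often as other patients convert. In the opposite extreme they never can, and the counted rate is p(1 − b). Correct selection is then 13.3% (b = 5%) or 13.0% (b = 10%) in the 65% scenario, with wrong selection 8.4% or 8.9%. In the 80% scenario it is 29.0% or 27.5%, with wrong selection 3.3% or 4.0%.

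**The case against.** The strongest reply is that the analysis compares randomized arms. Pre-existing reactivity is balanced in expectation, so a reader who infers systematic bias between arms or an inflated false-positive rate goes too far: step 4 shows type I error near 4% with either score. This stands.

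A reader might also infer that one pre-reactive patient necessarily supplies half of the deciding gap. The document does not support that. The patient changes the count only if vaccination would not have immunized them anyway, which is why step 2 falls from 71–92% to 33–56%. Moreover, *Immunologic efficacy* defines no responder, and *Sample size* does not say that the post-only score defines an immune response. That link is an inference from the two sections together with *Trial design and statistical considerations*, and the DTH-development wording could be read as new reactivity. The selection figures depend on it.

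A third tempting argument is that 0–5 mm is graded 1, so that an unreactive patient carries a floor that subtraction would remove. This should not be used. A floor common to all patients does not affect a rank test, and the normalization formula is not given; the obvious candidate, grade × 100/dose, cannot produce the zero of the stated scale.

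Finally, baseline correction has drawbacks. Leukapheresis precedes vaccination, so in the IFN-α arms day −1 comes after IFN-α, which the rationale expects to alter tumor immunogenicity. Subtraction might remove part of that effect. Strongly pre-reactive patients may have no room to rise on a scale capped at 80. These drawbacks limit the gain and must be stated. They do not justify leaving the measurement unused.

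**Conclusion.** The point holds as a mismatch between the stated aim and the fixed variable: the DTH score cannot tell induced from pre-existing reactivity, although the data to do so are collected in every patient. The consequences are misclassification, chance imbalance with six per arm and a modest loss of power.

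At 5–10% pre-reactive, correct selection drops by 1 to 2 percentage points at the plan's 15-point difference, and by about 3 to 5.5 points at a 30-point difference. Wrong selection is essentially unchanged and stays within the plan's 10% limit. These sizes rest on an assumed prevalence, on independence of pre-reactivity and conversion, and on the gap rule using the post-only score. If pre-reactivity is rarer than 5%, the effect is smaller still. The correction is worth making because it aligns the variable with its aim at almost no cost.

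**What to change.** Amend *Immunologic efficacy* and *Sample size* as follows.

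1. For each antigen (ATL, KLH), take the best post-treatment normalized score minus the patient's own day −1 normalized score. Analyse the larger of the two changes as the single score.
2. For the gap rule, count an immune response only if the post-treatment score exceeds the day −1 score for that antigen.
3. Keep the post-only best score as a sensitivity analysis.
4. State that in the IFN-α arms day −1 is a pre-vaccine rather than a pre-intervention baseline, and that strongly pre-reactive patients may be unable to show an increase because the scale is capped at 80.

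No extra test or visit is needed, since the day −1 DTH is already scheduled for all patients. The cost is the wording plus the two limitations in item 4.
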